### Approval and registration

The study was approved by Lund regional ethical review board, registration number 2010/330, and registered at ClinicalTrials.gov, registration number NCT01187576.

## Discussion

The targeted patients – individuals with newly diagnosed type 2 diabetes or hypertension – belong to a patient category that is indeed supposed to benefit from increased physical activity in terms of improved health variables, decreased risk of complications [27], and possibly also a decreased need of pharmacological therapy [42]. In the present study we combine a patient-centered lifestyle modification by a multi-professional team; a theory-based approach for self-regulation and behavior change; a feedback system for immediate response to treatment and adherence to treatment; and determination of cost-effectiveness of the intervention. This is in agreement with current guidelines for the prevention and management of the targeted diseases [5,6], and may increase the efficiency of treatment and evaluation of intervention.

The intervention intends to increase the patients’ internal motivation for physical activity by following the principles of SDT and MI, and thereby improve their adherence to PAR. The ultimate goal is to decrease cardiovascular complications, improve quality of life and work ability and decrease the need of medication. Our hypothesis is that the proposed PAR intervention is a more effective way to support patients in achieving and maintaining a beneficial level of physical activity than treatment as usual. We also believe that this structured intervention can be cost effective if it leads to a better health status and, subsequently, a less need of medical care among these patients.

The reason for using two control groups is that we believe there is a risk that the patients in Control group A may get an increased awareness of physical activity and subsequent alteration of habits, just by participating and filling in the questionnaires. Therefore we are also making a retrospective analysis at a third centre.

The study has some limitations. One possible limitation is the uncertain generalizability of the findings if the results of the intervention are related to individual qualities of the persons delivering the intervention, such as a special expertise and enthusiasm. Other possible limitations of lifestyle intervention studies in general and physical activity interventions in particular are the difficulties to determine relevant differences between the groups for the power calculation. The assumed difference of 200 MET-minutes is an ambitious goal and a balance between assumed effect of intervention, time to follow-up, and assumed number of patients. The primary outcome may not turn out significant at the first analysis (after one year). We believe, however, that 200 MET-minutes is a reachable difference and that the difference between the groups will increase over time.

If the extended PAR intervention proves to be successful, the model may be adopted by other primary care centers as well. Our goal is to find an attractive, user-friendly and cost effective PAR scheme, which may be translated to a broad range of patient groups that benefit from increased physical activity.

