## Background

The present protocol describes the trial design of a Swedish primary care intervention cohort study, which examines whether an extended, multi-professional physical activity referral (PAR) intervention is more effective in enhancing and maintaining the level of physical activity than physical activity prescription in usual care. The target group is patients with newly diagnosed type 2 diabetes and/or hypertension. The study is designed as a long-term intervention with recurrent analyses of self-reported physical activity levels as well as the effects of physical activity on health-related variables and cost-effectiveness.

Hypertension and type 2 diabetes belong to the major risk factors for cardiovascular disease that can be modified by a change in lifestyle, such as increased physical activity [1-3]. Several studies confirm that physical activity reduces the systolic and diastolic blood pressure in patients with hypertension, and improves the glycemic control in subjects with type 2 diabetes [2,4]. The evidence suggests that lifestyle modifications and exercise therapy are as effective as pharmacological treatment in selected cases. According to current guidelines, lifestyle modifications should be the first-line treatment alternative for patients with diagnose, or risk for, type 2 diabetes or hypertension [5,6]. Daily or almost daily aerobic physical activity of moderate intensity, such as brisk walking or swimming, for at least 30 minutes is recommended for both conditions [5-7].

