### Outcome measures

#### Primary outcome

Level of self-reported physical activity (as assessed with the International Physical Activity Questionnaire (IPAQ) and expressed as MET-minutes).

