### Statistical analysis and power calculation

The first statistical analyses and compilation of results will be performed 18 months after inclusion of the first patient or when the Intervention group and Control group A have included and followed up 60 and 30 eligible patients respectively for at least six months. At that point, data will also be collected retrospectively in control group B. Reasons for non-attendance in the study will be analyzed as well as reasons for non-adherence to the intervention. Allocation will be concealed, and study data blinded, for the bio-statisticians and researchers who will perform the analyses.

The sample size is based on an assumed statistical power of 80%, a significance level of 5%, a difference of 200 MET-minutes between the groups, a standard deviation of 300 MET-minutes and a worst-case loss to follow-up of 30%.

The secondary outcomes blood pressure, plasma glucose, need of pharmacological therapy, and cost-effectiveness will be compared between all three study groups.

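### The primary outcome has no fixed assessment time, the first analysis is dated inconsistently, and no one of the repeated analyses is named as confirmatory

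*Protocol article*

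**What the plan says.** All references are to the protocol article.

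- **Outcome (Primary outcome).** The definition is "Level of self-reported physical activity (as assessed with the International Physical Activity Questionnaire (IPAQ) and expressed as MET-minutes", with no time of assessment.
- **Number of analyses (Background; Methods/design).** The Background plans "recurrent analyses of self-reported physical activity levels". Methods/design repeats the intention over several years. The variable analysed is the primary outcome. No number of analyses is given, and End of study sets no closing date.
- **First analysis (Statistical analysis and power calculation).** It "will be performed 18 months after inclusion of the first patient or when the Intervention group and Control group A have included" and followed 60 and 30 patients respectively for a minimum of six months.
- **First analysis (Discussion, limitations).** "The primary outcome may not turn out significant at the first analysis (after one year". The authors go on to say that they believe the target difference is attainable and that "the difference between the groups will increase over time".
- **Error level (Statistical analysis and power calculation).** One level is given, as an input to the sample size: "a significance level of 5" per cent. It is not stated to be one- or two-sided.

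**The concern.** A confirmatory result needs one outcome, at one time, in one analysis. Here the outcome has no time, and the article dates the first analysis in two ways. It also says in advance that a non-significant first result would leave room for a larger difference later. With the study open-ended and further analyses of the same variable planned, a reader of a later positive report could not tell whether its time point was fixed beforehand or chosen once the data were known.

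The first aim is at stake: whether the extended referral raises and sustains activity. If more than one look may support that claim, the stated 5% need not be the chance of a false positive for the trial as a whole.

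**Working it through.** **1. The timing statements side by side.** The statistics section offers two triggers. Under the calendar trigger (18 months from the first enrolment) with continuous recruitment, an individual's follow-up could be anything from almost nothing to 18 months. Under the follow-up trigger, each counted patient has six months or more. The Discussion's one year has no stated starting point.

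- Counted per patient, it does not match a six-month minimum.
- Counted from the first enrolment, it does not match 18 months. It would match the second trigger only if all 90 patients were enrolled within the first six months, which the article does not say.

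Neither reading gives the primary outcome a time.

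**2. What the group sizes imply about the 5%.** The inputs, from the statistics section, are: "The sample size is based on an assumed statistical power of 80" per cent, "a difference of 200 MET-minutes between the groups", SD 300 and 30% loss. The 60 and 30 are the only group sizes given, and the text does not label them as the sample size. For 2:1 allocation under the normal approximation:

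n(control) = (1 + 1/2) × [SD × (z_alpha + z_power) / difference]²

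- One-sided 5%: 1.5 × [300 × (1.645 + 0.842) / 200]² = 20.9 controls and 41.7 intervention. Divided by 0.7, this is 29.8 and 59.6, that is **30 and 60**, so the figure is reproduced.
- Two-sided 5%: 27 and 54 before loss, 39 and 78 after. Not reproduced.
- 1:1 allocation: 52 per group two-sided or 40 per group one-sided, after loss. Not reproduced.

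Of these variants, only the one that spends the whole 5%, one-sided, on a single comparison returns 60 and 30. Because sidedness is not stated, this is an inference.

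**3. Power at these sizes.** Power = Φ(difference / SE − z_alpha), with SE = 300 × √(1/n₁ + 1/n₂).

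| Evaluable | SE | One-sided 5% | Two-sided 5% |
|---|---|---|---|
| 42 and 21 (60 and 30 less 30%) | 80.2 | 80.2% | 70.3% |
| 60 and 30 | 67.1 | 90.9% | 84.6% |

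**4. Overall error if every look used an unadjusted two-sided 5%.** The number of looks and the correlation between them are not in the document and are assumed. The independent case is 1 − 0.95^K; the others were simulated with 1,000,000 replicates.

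| Looks (K) | Same patients, correlation 0.9 | Same patients, correlation 0.5 | Accumulating data, equal steps | Independent (upper bound) |
|---|---|---|---|---|
| 2 | 7.0% | 9.0% | 8.3% | 9.75% |
| 3 | 8.4% | 12.6% | 10.7% | 14.3% |
| 5 | 10.2% | 18.3% | 14.2% | 22.6% |

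One-sided tests on accumulating data give 8.0%, 10.1% and 12.9% for two, three and five looks.

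**5. Price of a second confirmatory look.** Splitting a one-sided 5% equally over two looks gives 2.5% each. That needs about 78 and 39 enrolled. Otherwise power at 42 and 21 evaluable falls from 80% to 70%.

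**The case against.** A reader might infer that the plan retests the primary outcome at 5% until it succeeds, so that the error rate is already broken. The document does not support that. The 5% appears once, as a sample-size input, and no section says that later analyses use it, unadjusted or otherwise. The Discussion passage is a limitations paragraph: it says the first result may not be significant and records a belief about later growth. It sets no decision rule.

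There is also a benign reading. The first analysis may be the powered one, as the match of 60 and 30 to a single comparison suggests. The recurrent analyses, listed together with health variables and cost-effectiveness, may be descriptive monitoring. The aim includes maintaining activity, so later data partly answer a different question. The number of looks and any division of alpha are details that an article commonly leaves to the full plan, and the visit schedule is in a figure that is not shown.

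These points remove the claim that 5% is demonstrably not held. They do not settle the rest. The benign reading has to be supplied by the reader, because no analysis is called confirmatory. The two timing statements stand in the article itself and need reconciling whatever a separate plan contains. And the article presents a non-significant first result as open to change, which fits poorly with that result being final.

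**Conclusion.** The point holds as a failure to fix the confirmatory analysis, not as a demonstrated loss of error control. Three parts rest directly on the text: the primary outcome has no time, the statistics section and the Discussion do not agree on when the first analysis falls, and repeated analyses of that outcome are planned with none named as decisive. Nothing in the document prevents a positive claim from any look.

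The size is conditional. With later looks at an unadjusted two-sided 5%, overall error would be about 7% to 10% for two looks and about 10% to 23% for five. These are ranges over assumed numbers of looks and correlations, not properties of the plan. If the one-sided reading of the sample size is right, the first comparison uses the whole 5% and leaves none for later ones.

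**What to change.** - Name one confirmatory comparison: Intervention group against Control group A, IPAQ MET-minutes per week, at one fixed follow-up time per patient. Twelve months would fit the Discussion. Put that time in the outcome definition, and make the statistics section and the Discussion agree with it.
- Report all earlier and later analyses as estimates with confidence intervals and no confirmatory claim. If a second confirmatory look is wanted, fix the number of looks and an alpha-spending rule in advance and recompute the sample size.
- State the sidedness behind the sample size, say whether 60 and 30 are enrolled or evaluable, and restate the power to match.

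The text change is a few sentences, but it has a price. The confirmatory read-out may come later than the six-month trigger, and later looks lose confirmatory status. The stated power may also prove less favourable: a two-sided test with 60 and 30 enrolled and 30% loss has about 70%, and restoring 80% would need about 78 and 39 enrolled. The change should be made before the first analysis, since a time point named afterwards would carry little weight.

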## Abbreviations

ADL: Activities of daily living; BMI: Body mass index; CA: Control group A; CB: Control group B; ECG: Electro cardiography; fP-glu: Fasting plasma glucose; IG: Intervention group; IPAQ: International physical activity questionnaire; MET: Metabolic equivalent; MI: Motivational interviewing; PAR: Physical activity referral; SDT: Self-determination theory.
